### Website development

The content of the website will be based on several resources: (1) the FAB and members of the investigative team will advise on the content that should be included and develop all necessary informational sections; (2) a literature review; and (3) a review of existing sleep-related websites and brochures including the AASM, the NHLBI, and the NSF. The FAB will review the content for accuracy and completeness. The content will then be presented to the CSC, which will provide additional suggestions and comments; these will be incorporated into the final content used in the website. The investigative team will review the content to assess health literacy including ease of use, design layout, and readability. We will use the Flesch-Kincaid readability formula and the material will be customized at the fifth-sixth grade reading level.

### Tracking and Internet metrics

The website will be password-protected, accessible only by participants in the exposure arm. By providing a specific password to each participant, we will be able to track their activity on the site using Google Analytics logfile data and relate it to other participant characteristics. Google Analytics is a web analytics service offered by Google that tracks website usage and traffic. We will use this resource to ascertain how participants use the website by linking their login details with metrics generated by Google including pages visited, duration of time on each page, and frequency of visits to the website.

### Role model storytelling development

The primary vehicle by which the project will achieve its goal is through role model storytelling video vignettes. Evidence suggests that video presentation of OSA materials to patients with low literacy skills helped improve OSA knowledge (66% vs. 43%) and usage of continuous PAP (94% vs. 78%) [40]. Video vignettes acquired from interviews with black patients with OSA will demonstrate how poor sleep affects one’s daily functioning and overall health and quality of life; barriers and facilitators to adhering to OSA treatment; undergoing an overnight in-lab and in-home sleep study; and discussing treatment options with a sleep provider. We will use Taylor’s model as the framework guiding the role model story development. According to Taylor’s model [28], role model stories are effective if they reflect realities of individuals from the community to which they are directed. To be credible, the role model will reflect the race, culture, and socioeconomic circumstances of community members. Thus, the appropriate role model will be someone from that community who has adopted recommended healthful practices to be modeled in the story. Thus, initially potential role models recruited from the community will be screened in order to determine if the person could provide enough information about his/her experiences to create a role model story.

### Heurestic testing and tailoring

All role model stories and video vignettes included in the TASHE website will be pretested before randomization. We will conduct heuristic evaluation, led by a member of the investigative team, and cognitive walkthroughs of all web materials, and then perform standard formative usability testing with eight to ten representative participants to ensure the site is well-suited to the needs of the intended community. We will draw upon the work of Kreuter and colleagues [41] that outlines several steps on the way toward the design of tailored materials for health promotion activities. Developing tailored materials is an iterative process whereby participant and population needs are identified, formative materials are designed, feedback from the community or population is obtained, then another round of edits are made before materials can truly be termed ‘tailored’. After the opinions, attitudes, and beliefs about sleep and OSA specific to the population are ascertained, the website will be available for the intervention.

Data obtained from the usability testing include qualitative data obtained from the interviews, as well as quantitative metrics obtained from the computer-tracking software. The data analyst will conduct a qualitative analysis to identify themes in the participant reactions and comments. In addition, the quantitative data collected vis-à-vis the software program will be analyzed using statistical software. Descriptive analysis for the various quantitative metrics will be tabulated to understand the various website components that drew the most attention from participants.

### Focus groups

For aims 1 and 2 of this study, the focus will be on determining barriers preventing uptake of healthful sleep practices in the partner community and developing health messages to promote uptake of these practices. Barriers will be elicited through focus groups, and tailored health messages will be developed and refined. We will conduct five focus groups with patients and community stakeholders. In the first three groups, we will document barriers and factors facilitating or inhibiting uptake of healthful sleep practices. Emergent themes will be presented to the next two groups; here, the primary focus will be on reactions to these themes. Targeted themes will include beliefs, knowledge, values about healthful sleep practices, and mediating or reinforcing factors associated with healthful behavior. We will also conduct focus groups with community stakeholders and with healthcare providers. The purpose of the stakeholder focus group will be on reactions to health messages developed based on themes emanating from focus group with participants in aim 1. During the provider interviews, we will gauge their understanding of participants’ perspectives on benefits and harms of preventive, diagnostic, therapeutic, or sleep healthcare delivery systems. These factors influence participants’ decision-making regarding uptake of healthful practices.

### Eligibility criteria

Participants must meet the following study criteria: inclusion criteria: self-reported race/ethnicity as African American, African, Caribbean American or black men and women; ages ≥18 years; accessible by telephone; no plans to move away from the region within the year following enrollment; consent to participate, which includes permission to release medical record information; documented OSA risk based on scores received from the Apnea Risk Evaluation System (ARES) questionnaire [42]. Internet access is not an eligibility criterion, as participants will receive an iPad with cellular service.

Exclusion criteria will include: progressive medical illness in which disability or death is expected within 1 year; impaired cognitive or functional ability which would preclude meaningful participation in the study; sleep apnea diagnosis; stated intention to move within the same year of enrollment.

### Recruitment

We will use several recruitment strategies. First, we will utilize a recruitment funnel that we have developed from several other Institutional Review Board (IRB)-approved NIH-funded studies related to sleep health. Participants will be contacted via phone to ascertain their level of interest. If participants express interest, they will be invited to come to our office at New York University. Then, a member of the research team will provide detailed information about the study protocol, and read the consent form. Participants will have time to ask questions.

Second, we will host information sessions with prospective participants. These sessions will last approximately 20 minutes and will be led by a senior member of the investigative team. The purpose of the session is to (1) provide detailed information about the study protocol, (2) discuss requirements and expectations of participants, and (3) ascertain interest in moving forward with the study. Participants will receive information materials and a consent form that they may take home to discuss with their family, friends, or doctor, before they agree to sign the consent form. This will allow participants enough time to make an informed decision about whether or not to participate in the study. Participants will have time to answer questions of the investigative team.

Third, we will rely on established relationships with community-based and faith-based organizations including barbershops and churches. Through these efforts, the research team is able to go on site to gauge participant interests. We will follow the same procedures throughout the study, which involve: (1) providing detailed information about the study, (2) providing study materials for participants to review on their own time, and (3) allowing participants enough time to ask questions freely.

Finally, recruitment materials including flyers, brochures, and fact sheets will be developed in conjunction with the CSC. These materials will be at the fifth-sixth grade reading level. All materials provide an overview of what is involved in participating in the study, and will be placed in community venues including barbershops, community-based organizations, and churches. The CSC members will provide feedback to ensure that the materials are clearly written, and that they are acceptable to the community. The Project Manager in consultation with the Principal Investigator (PI) will oversee recruitment and consent.

### Allocation

Individuals will be eligible for randomization once their baseline questionnaire is completed. Randomization will be carried out in pairs using a table of random permutations conducted by the Program Manager. One member of each pair will be assigned to the Internet-based group and the other to the control group, using sealed envelopes. This strategy ensures equal allocation to the two groups, and that both have similar characteristics regarding measured and unmeasured background variables (i.e., patient characteristics and lifestyle behavior at baseline, medical comorbidities, and situational/contextual factors), which could potentially affect study outcomes. The Program Manager will hold the sequence of assignments and will dispense the code for each new patient upon request by the Research Assistant (RA). If a participant requests to be withdrawn from the study, the Program Manager will assign the code for the next new patient. The Program Manager  will maintain a record of who was randomized to which group to maintain integrity of planned analysis. Due to the nature of the study, the Program Manager will not be blind to the study arms. Randomization will be ongoing until sample size goals are reached: 100 per study arm and in accordance with the CONSORT randomization guidelines as shown in Fig. 2.

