Both selection and attrition biases might occur during data acquisition for aim 3. Selection bias might result from participant’s refusal to participate and attrition bias could result in an unbalanced design. Appropriate statistical techniques (e.g., Heckman two-stage approach GEE probit model, and Monte Carlo [53] will be used to address such biases, or problems that might result from missing data. Adequate statistical corrections will be made in final statistical analyses to increase generalizability of the findings. Sociodemographic data obtained from those who did not participate will be used to determine whether they are similar to those in the study [54]. Likewise, baseline characteristics of participants who withdrew from the study will be contrasted with completers to determine whether any attrition bias may have occurred.

The Biostatistician will manage study data under the PI’s supervision. He will create computerized data collection forms to ensure integrity and accuracy of data entry. He will help to minimize the problem of missing data by resolving omissions and errors as they arise. Throughout the study, the PI will oversee data entry and verification, ensure adherence to coding, and clean and edit protocols. Participant-identifying information will be kept in a locked file cabinet with only numerical identifiers in computer files.

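### On its most natural reading, the withdrawal rule reissues a used code to the next new patient, so that entry is neither randomly allocated nor concealed

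*Protocol article*

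**What the plan says.** All the operative text is in the protocol article under Allocation.

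- Method: "Randomization will be carried out in pairs using a table of random permutations conducted by the Program Manager". One member of each pair goes to each arm, by sealed envelope.
- Ordinary case: "The Program Manager will hold the sequence of assignments and will dispense the code for each new patient upon request by the Research Assistant (RA".
- Withdrawal: "If a participant requests to be withdrawn from the study, the Program Manager will assign the code for the next new patient".
- Record: the Program Manager "will maintain a record of who was randomized to which group to maintain integrity of planned analysis".
- Blinding: "the Program Manager will not be blind to the study arms".
- End of enrolment: "Randomization will be ongoing until sample size goals are reached: 100 per study arm".

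Under Statistical analysis, the article adds that "baseline characteristics of participants who withdrew from the study will be contrasted with completers to determine whether any attrition bias may have occurred", and it names several techniques for attrition bias and missing data without choosing among them. It does not say whether a code can be used twice, whether a withdrawn participant counts toward the 100, or that participants are analysed in the arm to which they were randomised.

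**The concern.** A randomisation code should be spent once. If a withdrawal releases a code for reuse, a post-randomisation event in one person decides the arm of another. The Allocation section justifies the pair scheme by saying it balances measured and unmeasured characteristics. A reissued code does not carry that guarantee, because it does not come from the next place in the random sequence.

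Concealment is also at stake. The arm attached to a used code is already known, so whoever knows it can foresee the next patient's arm and could, knowingly or not, influence who enters next or when. The trial is listed as recruiting, so the rule may already be in use, and an assignment made this way cannot be re-randomised later.

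**Working it through.** **1. Reading the sentence.** Two readings are possible.

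| Reading | What a withdrawal triggers | Arm of the next new patient |
|---|---|---|
| A. The withdrawn person's code goes to the next new patient | Reuse of a spent code | Fixed by who withdrew |
| B. The next new patient gets the next code in the sequence | Nothing new | Set by the random sequence |

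Under B the sentence repeats the ordinary case just before it, and its condition (a request to withdraw) does no work. Under A it adds a rule. A is therefore the more natural reading, but B is not excluded.

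**2. What A does to one entry.** Suppose all pairs so far are complete and a participant in the Internet-based arm withdraws. Under B the next patient opens a new pair and has probability 1/2 of each arm. Under A the probability of the Internet-based arm is 1. The envelope for that code has already been opened, so sealing no longer protects it.

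**3. How many entries could be affected.** The document gives no withdrawal rate, so 5% to 30% is assumed. If N people enter, a fraction d withdraws and every withdrawal is replaced until 100 per arm remain, the number entering per arm is 100/(1 − d), rounded up, and the excess over 100 is the number of reissued codes.

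| d | Entering per arm | Reissued per arm | Reissued, both arms | Share of all entries |
|---|---|---|---|---|
| 5% | 106 | 6 | 12 | 12/212 = 6% |
| 10% | 112 | 12 | 24 | 24/224 = 11% |
| 20% | 125 | 25 | 50 | 50/250 = 20% |
| 30% | 143 | 43 | 86 | 86/286 = 30% |

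Apart from rounding, the share equals d. These are upper bounds: they assume that withdrawals do not count toward the 100 and that all of them happen before enrolment closes. Later losses cannot be replaced.

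**4. Refilling.** If withdrawals are not counted and the rates differ, for example 20% against 10%, one arm takes 25 replacements and the other 12, while both end at 100. If the 100 counts participants randomised, no arm is refilled.

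**5. Does replacement itself bias the effect estimate?** This was simulated with no true effect, 6,000 runs per setting, baseline-outcome correlation 0.5, and withdrawal on the logit scale with slope −0.5 or −1 per SD of baseline literacy. Those who stayed were compared without adjustment. Mean spurious effect in SD (slope −0.5 / −1):

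| Withdrawal by arm | Without replacement | Replaced to 100 per arm |
|---|---|---|
| 20% vs 5% | 0.036 / 0.063 | 0.038 / 0.064 |
| 30% vs 5% | 0.056 / 0.106 | 0.062 / 0.102 |

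The columns agree within simulation error. With baseline literacy as a covariate the bias is at most 0.002 SD and the type I error 5.0% to 5.5%. These figures therefore describe generic differential dropout under assumed rates and an unadjusted test. They do not measure code reissue or loss of concealment.

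**6. The target.** The only figure tied to the rule is 100 per arm. The Sample size section's inputs (27% vs 40%, two-sided 5%, 85% power) give 236 per arm by the usual formula, not 100. That is a separate matter, and nothing here rests on it.

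**The case against.** The strongest reply is that the sentence never says the code is the withdrawn person's, or that it is reused. Read with the sentence before it, it may only mean that allocation carries on with the next patient's own code. That ambiguity is real and stands, but a rule that can be read as permitting reuse needs rewording under either reading.

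A second reply is that the Program Manager holds the whole sequence and so already foresees every arm. For that person this is fair. What reissue adds is that the arm no longer comes from the sequence at all, and that anyone who knows the withdrawn participant's arm can also foresee it.

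A reader might go further and infer that the trial becomes a comparison of those who stayed. The documents do not support this. No text excludes withdrawn participants from analysis, a record of randomised group is kept, attrition methods are planned, and withdrawn participants are compared with completers at baseline. A reader might likewise take the target as 100 retained per arm, but the sentence "Randomization will be ongoing until sample size goals are reached: 100 per study arm" governs randomisation and says nothing about retention.

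These provisions limit the inference without curing the rule. Keeping a record is not a commitment to analyse as randomised, and no later analysis makes a foreseeable assignment random.

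**Conclusion.** The concern holds in a limited form. On the most natural reading, each reissued code gives one patient an arm fixed by who withdrew and known in advance to the unblinded holder of the codes. The extent is at most the share of participants who withdraw before enrolment closes: up to 6% to 30% of entries if withdrawal is 5% to 30% and withdrawals are not counted toward the target. Those rates are assumptions.

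No size of bias in the treatment effect can be given. If withdrawal is unrelated to arm and nobody acts on the foreseeable assignment, the effect may be negligible. Weekly contact is described for the intervention arm only (Plans to promote retention), which makes unequal withdrawal plausible but does not show it. Refilling of the arm with more losses is conditional on a counting rule that the text leaves open.

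**What to change.** Replace the withdrawal sentence under Allocation with:

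> Each code is used once and is never reissued. A participant who withdraws keeps the assigned arm and is analysed as randomised. Each new participant receives the next unused code.

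State in the same section that the target of 100 per arm counts participants randomised. If any code has already been reissued, list those entries so that they can be identified in the analysis.

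The cost is wording, plus fewer than 100 completers per arm. With 95, 90, 80 or 70 remaining (5%, 10%, 20% or 30% loss), standard errors grow by √(100/remaining), that is by 3%, 5%, 12% or 20%. If 100 completers per arm are wanted, set the number randomised higher in advance (106, 112, 125 or 143 per arm at those rates) and do not replace withdrawals.

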**Fig. 2 Fig2:**
[figure not shown]
CONSORT flow diagram

### Measures

Screening of baseline measures: we estimate that completion of the baseline study measures will take up to 15 minutes. For participants who are eligible and enrolled into the study, we estimate that the additional screening questionnaires will take up to 30 minutes.

#### Sociodemographic variables

Sociodemographic variables will include age, type of health insurance, marital status, education, number of children living in household, number of adults living in household, employment status, and annual household income.

#### Apnea Risk Evaluation System questionnaire

The ARES includes questions on sleep patterns, daytime functioning, knowledge of sleep apnea, and diseases associated with sleep apnea [that is, hypertension (HTN), diabetes mellitus (DM), heart disease] [42].

#### Epworth Sleepiness Scale

The Epworth uses a Likert-type scale in which the respondent indicates the most appropriate number ranging from 0 = would never doze or sleep to 3 = high chance of dozing or sleeping based on a given situation. A score of 10 or more is considered excessive sleepiness [43].

#### Apnea Knowledge Test (AKT) [44] and Apnea Beliefs Scale (ABS) [44]

These two questionnaires measure participants’ understanding and beliefs of obstructive sleep apnea and CPAP treatment. The AKT includes 13 questions with a yes/no response choice and two open-ended questions; the ABS includes 24 items on a five-point Likert scale ranging from “strongly agree” to “strongly disagree”. A higher score on the AKT indicates better knowledge and understanding of the illness and treatment and a higher score on the ABS indicates greater likelihood of adherence to treatment [44].

#### Change Assessment Scale (CAS)

The CAS is a 32-item instrument that assesses a person’s readiness to change. Participants evaluate the extent to which they strongly agree or strongly disagree with various statements such as, “I’ve been thinking that I might want to change something about myself” and “I have problems and I really think I should work on them.”

#### Medical history

Medical history includes family history of sleep disorders, obesity, DM, HTN, dyslipidemia, and CVD; history of other preventive behaviors (for example, prostate examinations), and other health behaviors (for example, regularity of physical examinations, cholesterol screening, smoking and drinking habits, and exercise habits) [45].

#### Sleep Hygiene Index (SHI)

The SHI is a 13-item instrument that measures sleep hygiene behaviors. It was derived from the diagnostic criteria for inadequate sleep based on the International Classification of Sleep Disorders. Participants are asked about the frequency that they engage in specific behaviors with a response of “always,” “frequently,” “sometimes,” “rarely,” or “never.” Behaviors such as using the bed for things other than sleeping and sex, and daytime naps longer than 2 hours are included [46].

#### Short Test of Functional Health Literacy in Adults (S-TOFHLA)

The S-TOFHLA is a measure of a patients reading and comprehension of both print and numeracy health-related information [23].

#### Sleep Apnea Literacy Scale

This is a 24-item instrument designed to measure patient-level knowledge, efficacy, and literacy barriers to effective treatment for sleep apnea. Specific items include statements such as “when breathing stops during sleep this is called sleep apnea” and “poor concentration can be caused by sleep apnea.” Participants are asked to mark their confidence for these statements about sleep apnea on a scale from “very confident this is true” to “not at all confident this is true” [47].

